# Emergence times and airway reactions in general laryngeal mask airway anesthesia: study protocol for a randomized controlled trial

**DOI:** 10.1186/s13063-015-0855-2

**Published:** 2015-07-26

**Keywords:** laryngeal mask airway, emergence time, airway reaction, anesthesia

## Abstract

**Background:**

The use of a laryngeal mask airway (LMA) in appropriate patients supports fast-track anesthesia with a lower incidence of postoperative airway-connected adverse events. Data on the most favorable anesthetic in this context, with the lowest rate of upper airway complications and fast emergence times, are controversial and limited. Desflurane seems to match these criteria best, but large randomized controlled trials (RCTs) with a standardized study protocol are lacking. Therefore, we aim to compare desflurane with other commonly used anesthetics, sevoflurane and propofol, in a sufficiently powered RCT. We hypothesize that desflurane is noninferior regarding the frequency of upper airway events and superior regarding the emergence times to sevoflurane and propofol.

**Methods/Design:**

A total of 351 patients undergoing surgery with an LMA will be included in this prospective, randomized, double-blind controlled, multicenter clinical trial. The patients will be randomly assigned to the three treatment arms: desflurane (*n* = 117), sevoflurane (*n* = 117), and propofol (*n* = 117). The emergence time (time to state the date of birth) will be the primary endpoint of this study. The secondary endpoints include further emergence times, such as time to open eyes, to remove LMA, to respond to command and to state name. Additionally, we will determine the frequency of cough and laryngospasm, measured intraoperatively and at emergence. We will assess the postoperative recovery on the first postoperative day via the Postoperative Quality Recovery Scale.

**Discussion:**

Despite increasing importance of cost-effective and safe anesthesia application, we lack proof for the most advantageous anesthetic agent, when an LMA is used. There are only a few RCTs comparing desflurane to other commonly used anesthetics (sevoflurane, propofol and isoflurane) in patients with LMA. These RCTs were conducted with small sample sizes, huge interstudy variability, and some also showed strong biases. The present multicenter RCT will provide results from a large sample size with a standardized study protocol and minimized bias, which is feasible in the clinical routine. Furthermore, we will expand our knowledge regarding the most favorable recovery on the first postoperative day, which impacts patients’ comfort after surgery.

**Trial registration:**

EudraCT Identifier: 2014-003810-96, 5 September 2014

ClinicalTrials.gov: NCT02322502, December 2014

**Electronic supplementary material:**

The online version of this article (doi:10.1186/s13063-015-0855-2) contains supplementary material, which is available to authorized users.

## Background

### Background and rationale

Fundamental pillars of anesthesia care are the safe and measured application of anesthesia. Improvement of facility and resource utilization with a high patient turnover and early discharge of patients from the operating room and hospital is becoming increasingly important. This hinges on a rapid emergence and early recovery from anesthesia. Desflurane’s low blood gas coefficient supports general anesthesia (GA) in a fast-track technique, even in obese patients [1]. The use of a laryngeal mask airway (LMA) attenuates the risk of postoperative airway-connected complications in comparison to endotracheal tubes (ETT) in GA [2].

Desflurane’s possible airway irritant properties compared to other anesthetics like sevoflurane, propofol and isoflurane are still the subject of discussions [1]. However, studies comparing the risk of intraoperative upper airway adverse events like cough and laryngospasm (LS) vis-à-vis other common anesthetics are limited. One meta-analysis [3] considered these adverse events in patients with LMA and could not evince a greater incidence with desflurane compared only to sevoflurane anesthesia. Data regarding recovery times were not assessed in this meta-analysis. Therefore, we have recently performed a further meta-analysis [4] comparing desflurane’s properties to other commonly used anesthetics with LMA: isoflurane, sevoflurane and propofol. We identified only 13 randomized controlled trials that have analyzed the variables of upper airway adverse events (intraoperative cough (CO), cough at emergence (CE) and laryngospasm (LS)) and the recovery times (time to open eyes (TOE), to remove LMA (TLR), to respond to command (TRC) and time to state date of birth (TSB)). While the frequency of upper airway adverse events did not differ between the analyzed anesthetics, the recovery times in the desflurane groups were superior to the other anesthetic groups. The variable CO showed a non-significant RR (95 % CI) of 1.12 (0.63, 2.02), (*P* = 0.70), between desflurane (*n* = 284) and all other examined anesthetic agents (*n* = 313). CE was only examined after desflurane (*n* = 148) and sevoflurane (*n* = 146) administration and also indicated no difference, RR [95 % CI] of 1.49 (0.55, 4.02), (*P* = 0.43). LS was rare and desflurane (*n* = 262) showed no difference when compared to all other analyzed anesthetics (*n* = 289), or when compared only to sevoflurane, RR (95 % CI) of 1.03 (0.33, 3.20), (*P* = 0.96). All emergence-time variables were significantly faster in the desflurane group. Due to the small sample sizes, huge study protocol distinctions and the fact that the examined variables were mainly secondary endpoints of the included studies, these findings have to be seen within their limits. Additional large randomized controlled trials are indicated to validate the results of our meta-analysis [5].

### Objectives and study design

This will be a multicenter, controlled, double-blind, randomized, three-arm parallel, interventional clinical study. The purpose of this study will be to assess the following:If desflurane is superior in achieving a faster emergence from anesthesia (when patient can state his/her date of birth).If desflurane is noninferior in the occurrence of upper airway complications compared to sevoflurane or total intravenous anesthesia with propofol in the setting of laryngeal mask airway.

### Specific primary objective

The specific primary objective is to determine the time of emergence from anesthesia with LMA (defined as time between cessation of anesthesia until patient is able to state his/her date of birth (TSB) on command) after desflurane compared to sevoflurane or propofol.

### Specific secondary objectives

The specific secondary objectives are to determine the frequency of airway reactions (CO, LS, laryngospasm at emergence (LSE) and CE) in patients undergoing desflurane anesthesia with LMA, compared to sevoflurane or propofol. Additionally, we will analyze further emergence times (TLR, TOE, TRC, time to state the full name (TSN) on command and the recovery index [6]) in the same patients after cessation of anesthesia.

### Other secondary objectives

Other secondary objectives are to determine the influence of gender on the patients’ reactions, the anesthesia safety variables including hemodynamic stability, the frequency and quantity of postoperative nausea, vomiting and pain, the discharge times, the pharmacoeconomics and the recovery on the first postoperative day (1^st^ POD).

## Methods/Design

### Study setting

This multicenter study will be conducted in four German study centers (University hospitals of Aachen and Ulm and the regional hospitals of Reutlingen and Halle).

### Eligibility criteria

Investigators in each center will be selected and supervised by the local coordinating principal investigator. To ensure the blinding process, at least two investigators will be needed, when a patient is enrolled in this study. Therefore the screening and enrollment process will be performed according to the logistical possibilities of each center. All potential patients meeting the inclusion criteria will be documented in a screening log kept at each site. The reasons for not enrolling eligible patients will have to be stated in the screening log.

Inclusion criteria: A written informed consent prior to study participation will be mandatory. Participants in the study have to be adult patients between 18 and 75 years of age. They have to be scheduled to undergo elective surgery with a planned duration of 0.5 to 2 hours and the use of LMA. Both sexes will be included, and further inclusion criteria are an American Society of Anesthesiologists (ASA) physical status 1 to 3 and body mass index (BMI) <35 kg m^−2^.

Exclusion criteria: Subjects fulfilling one or more of the following exclusion criteria will not be included in the study: patients with planned additional regional and local anesthesia, with asthma or chronic obstructive pulmonary disease (COPD) grade IV, contraindication for the use of a LMA, known allergy or hypersensitivity to any drugs administered during this study. Furthermore, women who are pregnant, breast-feeding or of childbearing potential and not using adequate contraceptive methods will be excluded. Patients legally unable to give written informed consent, nonfluency in German language, with severe psychiatric or neuropsychiatric disorders or recent (<6 months) history of alcohol or drug abuse will not be included. The participation in a drug or device trial within the previous 30 days will be a further exclusion criterion.

### General interventions for all patients

Premedication: All patients will receive an oral administration of up to 7.5 mg midazolam 30 to 45 minutes preoperatively, according to the clinical routine of each center.

Induction: Upon arrival into the surgery room, a standard monitoring will be applied to all patients. This will consist of continuous electrocardiogram (ECG), measurement of non-invasive blood pressure (NIBP) and peripheral oxygen saturation (SpO_2_). A connection of Bispectral Index (BIS) monitoring will follow. After pre-oxygenation with oxygen (FiO_2_ = 1.0) for 3 minutes via face-mask, all patients will receive remifentanil injection via infusion pump at an initial rate of 0.5 μg kg^−1^ over 60 seconds and 1.5 to 2.5 mg kg^−1^ (plus 2 ml lidocaine 1 %) propofol by bolus titration intravenous (i.v.). After loss of consciousness, the LMA will be inserted and blocked with a cuff pressure at 30 cm H_2_O. Teeth marks on the device will help to check the correct insertion. The leakage will have to be controlled by applying a positive airway pressure of 25 cm H_2_O. A reassessment will take place after 5 minutes. If the LMA is not tight, a replacement of LMA will follow. After a second failure of LMA placement, an alternative airway will be applied.

Maintenance: All patients will receive a postoperative nausea and vomiting (PONV) prophylaxis with 8 mg dexamethasone and 4 mg ondansetron, if the Apfel-Score is ≥2. Analgesia will be maintained with remifentanil injection via infusion pump at a rate of 0.15 μg kg^−1^ min^−1^. Dosage will be adapted according to clinical needs based on the patient’s hemodynamic (difference of NIBP and HR greater than 20 % from baseline), autonomic (sweating, salivation, or flushing) and somatic (movement or swallowing) signs. Twenty minutes before the estimated end of surgery, all patients will receive 0.05 to 0.1 mg kg^−1^ piritramide and 15 mg kg^−1^ metamizole i.v. The inspired oxygen concentration will be adjusted to 35 to 50 %, or above this range if medically indicated. The end-expiratory CO_2_ level during the maintenance of anesthesia should be kept between 36 and 45 mmHg. The use of muscle relaxants is undesired, except for emergency situations. Spontaneous breathing or controlled ventilation with LMA will be applied during maintenance of anesthesia, according to the standard operating procedure of each participating center. Inspired desflurane concentrations of >8 vol. % and sevoflurane >2.2 vol. % have to be avoided. The systolic blood pressure should be kept at ≥90 mmHg (or ≥65 mmHg for mean arterial blood pressure), and a relative variation > 20 % from baseline values has to be avoided and requires appropriate treatment. If indicated additional bolus injection of propofol is permissible in patients.

End of anesthesia: At five minutes before planned termination of surgery, remifentanil will be discontinued. The LMA will be removed when the upper airway reflexes are fully recovered and the respiratory function is adequate (regular spontaneous breathing with a frequency of at least eight breaths per minute and SaO_2_ >95 %) and when the patient opens his/her eyes on request or is able to follow any other requests. In addition, the patient has to be hemodynamically stable before removal of LMA. The patients will be admitted to the Post Anesthesia Care Unit (PACU) following surgery. They will receive 0.05 mg kg^−1^ piritramide if the visual analog scale (VAS) for pain is more than 30.

### Specific interventions

There will be three parallel intervention groups receiving different anesthetics for the maintenance of anesthesia after the induction phase and placement of the LMA.

Group 1 will receive desflurane. After setting the fresh gas flow at 2l min^−1^, the desflurane vapor will be turned to 12 vol. % until the desired end-expiratory target concentration of 0.8 MAC (minimal alveolar concentration) or 4 to 5 vol. % desflurane is achieved. Thereafter, a reduction of the fresh gas flow to 500 to 1,000 ml will be performed to maintain anesthesia. Desflurane concentration will be adjusted to maintain a BIS index value between 40 and 60. Five minutes before estimated termination of surgery, the vapor will be set to zero. At the end of the surgery maximum fresh gas flow will be applied. This time-point will be defined as time zero (T_0_).

Group 2 will receive sevoflurane. After setting the fresh gas flow at 2l min^−1^, the sevoflurane vapor will be turned to 8 vol. % until the desired end-expiratory target concentration of 0.8 MAC or 1.2 to 1.4 vol. % sevoflurane is achieved. Thereafter, a reduction of the fresh gas flow to 500-1000ml will be performed to maintain anesthesia. Sevoflurane concentration will be adjusted to maintain a BIS index value between 40 and 60. Five minutes before estimated termination of surgery, the vapor will be set to zero. At the end of the surgery maximum fresh gas flow will be applied. This time-point will be defined as time zero (T_0_).

Group 3 will receive propofol via infusion pump at an initial rate of 5 to 7 mg kg^−1^ h^−1^ propofol and then adjusted to maintain a BIS index value between 40 and 60. Five minutes before estimated termination of surgery the propofol concentration will be halved. Propofol will subsequently be discontinued and maximum fresh gas flow with F_i_O_2_ = 1.0 will be applied at the end of surgery. This time-point will be defined as time zero (T_0_).

### Interventions - modifications

All drugs used in this trial are anesthetics used daily in the clinical routine of all participating centers. Harms are not anticipated in any study treatment. All possible side effects are described in the summary of medicinal product characteristics (SmPC). Other potential side effects and changes in the frequency of possible side effects are not expected during the trial. A modification or discontinuation of the assigned study intervention is not expected. In the event of modifications or discontinuations of the study treatment, study participants will be retained in the study to enable data collection and preclude missing data.

### Outcomes

#### Primary outcome measures

The primary objective of this trial is to investigate, whether the emergence time until the stating of the date of birth after desflurane anesthesia is superior to the time after sevoflurane or propofol anesthesia. The selection of stating the date of birth as the primary clinical outcome variable is associated with the result of our latest meta-analysis [4]. This meta-analysis supposes faster emergence times in the desflurane-treated patients, but the included studies had only small sample sizes ≤65 patients per group. Furthermore, they were not all powered for this outcome variable, and the study protocols were not standardized for all patients. The time to state the date of birth was chosen, since this variable requires the most conscious answer compared to the other emergence variables. This primary outcome time variable is defined as time between cessation of anesthesia (T_0_) until the patient is able to state his/her date of birth on command (given every 20 sec.) and will be measured in minutes and seconds.

#### Secondary outcome measures

The secondary outcome measures will be the determination of the following additional emergence times:Time to remove laryngeal mask (TLR)Time to open eyes on command (TOE)Time to respond on command to press hand (TRC)Time to state the full name on command (TSN)Recovery Index RI = 1 + Aldrete_5 min/[(2 x extubation time) + 1 x opening eyes time)]_ [6]

These secondary outcome variables will also be assessed in minutes and seconds after cessation of anesthesia (T_0_). Furthermore, we aim to analyze the frequency of upper airway events in desflurane-anesthetized patients compared to sevoflurane and propofol. These variables were also analyzed in our meta-analysis [4] and indicated that there were no distinctions between the anesthetics. According to the emergence times, the included studies had only small sample sizes and were not all powered for these variables. Our study is also powered to show a noninferiority of intraoperative coughs in desflurane versus sevoflurane and propofol anesthetized patients. The following upper airway events will be assessed:Frequency of intraoperative coughs, CO (induction/maintenance) - noninferiority designFrequency of intraoperative laryngospasm, LS (induction/maintenance)Frequency of cough at emergence, CEFrequency of laryngospasm at emergence, LSE

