### Sample size

Sample-size estimates for both considerations (superiority and noninferiority) were calculated separately. All sample sizes were calculated using a type 1 error, α = 0.05, and power of 0.80. The primary outcome calculations were carried out based on a one-way analysis of variance (same n) with three groups. The variances and means were estimated for the primary outcome variable time to state the date of birth from our meta-analysis [4]. For the sevoflurane, propofol and desflurane groups, means were set to 8.75, 6.8 and 5.6 minutes, respectively. A standard deviation of 3 minutes was considered (these parameters correspond to an effect size (f) of 0.43). A sample size of 19 patients per group is needed to detect such an effect for our superiority hypothesis.

The sample size for the noninferiority hypothesis was calculated based on the secondary outcome variable cough overall (CO). Using the normal approximation to the binomial and assuming a proportion of the outcome in the population between 0.07 and 0.10 and noninferiority bound of 0.20 a sample size of 81 and 112, respectively, is required to claim noninferiority. The margin delta of 20 % was chosen for clinical considerations. We claim that a difference of cough occurrence up to 20 % is clinically not relevant. This is justified by the result of our meta-analysis [4], where the identified coughs had never lead to a serious impact on the patients’ outcomes.

The sample size calculation for noninferiority of treatment is based on a sample size formula published by Blackwelder [7]. Considering data from the literature, a dropout rate of 5 patients per group (for example, requirement of endotracheal intubation, protocol deviations and losses for first postoperative day- follow up) is expected. We decided therefore to include 117 patients per group, to cover the calculated sample size of 19 + 5 patients per group for the superiority hypothesis as well as 112 + 5 patients for the noninferiority hypothesis. Altogether, there will be 351 randomized patients.

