### Statistical methods

All efficacy, safety and economical results will be presented on the Intention to Treat (ITT) data set, which will be composed of all randomized patients. In case it appears necessary, we will define a secondary Per Protocol (PP) data set prior to the database lock. The PP would be a subset of the ITT data set, composed of all randomized patients who have no major protocol deviations throughout their entire study period. This PP data set would be used for the secondary supportive analysis of the primary efficacy criterion and serve as a check of its robustness.

Parametric data will be analyzed with ANOVA and nonparametric data with the two-tailed Fisher’s exact test if incidence <5 or the Chi-square test with incidence >5. The inference for the noninferiority will be based on the upper confidence bound. A fully specified Statistical Analysis Plan will be made public before unmasking results. Additional analyses are not planned.

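### Noninferiority is claimed for upper airway events in general, but only intraoperative cough has a margin, a sample size and a noninferiority design

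*Protocol article*

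**What the plan says.** **The claim.** The second study purpose in the protocol article (Objectives and study design) is to assess: "If desflurane is noninferior in the occurrence of upper airway complications compared to sevoflurane or total intravenous anesthesia with propofol". The hypothesis in the Abstract is equally broad on endpoints but names the two comparators jointly. Specific secondary objectives lists four airway reactions: intraoperative cough (CO), intraoperative laryngospasm (LS), cough at emergence (CE) and laryngospasm at emergence (LSE).

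**The design.** Secondary outcome measures states: "Our study is also powered to show a noninferiority of intraoperative coughs in desflurane versus sevoflurane and propofol anesthetized patients". In the list that follows, CO alone is marked as a noninferiority endpoint. Sample size treats cough only: "All sample sizes were calculated using a type 1 error, α = 0.05, and power of 0.80", with the calculation "assuming a proportion of the outcome in the population between 0.07 and 0.10 and noninferiority bound of 0.20", and the result "a sample size of 81 and 112, respectively, is required to claim noninferiority". The margin is defended as an absolute difference: "We claim that a difference of cough occurrence up to 20 % is clinically not relevant". That section expands CO as overall cough, while the outcome list and the abbreviations define it as intraoperative cough; I take these to be one endpoint.

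**The analysis.** Statistical methods assigns Fisher's exact test (two-tailed) or the chi-square test to count data, and adds: "The inference for the noninferiority will be based on the upper confidence bound".

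**The concern.** The stated hypothesis and objective promise more than the design can deliver. A noninferiority conclusion needs a margin fixed in advance and a confidence bound to compare with it. For LS, CE and LSE there is no margin, so an upper bound has nothing to be judged against and only the difference tests remain. Non-significance there may reflect no more than few events.

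The risk is practical. Background and rationale reports a risk ratio for cough at emergence of 1.49 (95 % CI 0.55 to 4.02) and reads it as showing no difference, although the interval reaches a fourfold risk. If the trial's own results were read in the same way against the broad objective, desflurane could be called noninferior for laryngospasm or emergence cough without evidence.

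The comparators are a second loose end. With *or* in one place and *and* in two others, the text does not settle what a noninferiority claim against the comparators requires.

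**Working it through.** **Step 1: claim against design.**

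| Event | Under the broad objective | Marked noninferiority | Margin | Sample size |
|---|---|---|---|---|
| CO | yes | yes | 0.20 | 81 to 112 per group |
| LS | yes | no | none | none |
| CE | yes | no | none | none |
| LSE | yes | no | none | none |

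Three of the four events fall under the claim but outside the design. The cough margin cannot simply be carried over: its justification in Sample size is that coughs in the meta-analysis had no serious consequences, which says nothing about laryngospasm.

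**Step 2: reproduce the stated sample size.** Inputs from Sample size: α = 0.05, power 0.80, common proportion p = 0.07 or 0.10, margin δ = 0.20, Blackwelder's two-group formula. Assumptions: one-sided α (in keeping with an upper bound) and no true difference. The per-group size is

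n = (z₀.₉₅ + z₀.₈₀)² × 2p(1−p) / δ², with (1.645 + 0.842)² ≈ 6.183.

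- δ = 0.20, p = 0.07: 6.183 × 0.1302 / 0.04 = 20.1, so 21.
- δ = 0.20, p = 0.10: 6.183 × 0.18 / 0.04 = 27.8, so 28.
- δ = 0.10, p = 0.07: 6.183 × 0.1302 / 0.01 = 80.5, so 81.
- δ = 0.10, p = 0.10: 6.183 × 0.18 / 0.01 = 111.3, so 112.

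At one-sided 0.025 the sizes are 26 and 36 (δ = 0.20) or 103 and 142 (δ = 0.10). Of the variants tried, including unequal rates, a relative margin and a pooled formula with and without continuity correction, only δ = 0.10 at one-sided 0.05 gives the printed pair. The stated margin of 0.20 does not.

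**Step 3: power against one and against both comparators, 112 per group.** Single-comparison power is Φ(δ / √(2p(1−p)/112) − 1.645). The two comparisons share the desflurane arm, so with equal rates their correlation is 0.5; joint power is the bivariate normal probability that both succeed.

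- δ = 0.20, p = 0.10: 0.20 / 0.0401 − 1.645 = 3.34; single 0.9996, joint 0.999 (joint 0.998 at one-sided 0.025).
- δ = 0.10, p = 0.10: 0.10 / 0.0401 − 1.645 = 0.85; single 0.80, joint 0.69 (simulation with 400,000 runs: 0.71).
- δ = 0.10, p = 0.07: 0.10 / 0.0341 − 1.645 = 1.29; single 0.90, joint 0.83.

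For joint power of 0.80 at p = 0.10 and one-sided 0.05, 36 per group are needed at δ = 0.20 and 143 at δ = 0.10.

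**Step 4: the other events.** The protocol assumes no rates for them. If their rates lay between 0.10 and 0.50 (my assumption), joint power per event at 112 per group and one-sided 0.05 would run from 0.999 down to 0.85 at δ = 0.20, and from 0.69 down to 0.28 at δ = 0.10. So what rules out a noninferiority claim for these events as planned is the missing margin; whether the numbers would suffice depends on a margin nobody has set.

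**The case against.** The strongest reply is that the operative sections are already correct. The power sentence is confined to intraoperative cough, the noninferiority label sits on CO alone, and Specific secondary objectives speaks only of determining frequencies. On this view the Abstract and the objectives are loose summaries. This stands in part: the power sentence does not overreach on endpoints, and nothing says that a non-significant test will be read as noninferiority. But the broad wording is the trial's stated hypothesis and purpose, against which its conclusions will be read.

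A reader might also infer more than the documents support:

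- *That the power of 0.80 is overstated because two comparators are involved.* At the stated margin it is not; joint power is about 0.999. The shortfall to 0.69 needs a margin of 0.10, cough rates at the top of the assumed range, and a rule that both comparisons must succeed. The protocol states neither the first nor the third, and at p = 0.07 joint power is 0.83 even with margin 0.10.
- *That the type 1 error is inflated.* If success against either comparator were enough, the one-sided error would be about 8.8 % with both true differences at the margin. The *or* in the objective does not establish that rule, and two separately reported pairwise comparisons are an equally natural reading.
- *That the missing level of the upper bound is a defect.* That is ordinary SAP detail, and the protocol promises a public SAP before unmasking.

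**Conclusion.** The mismatch of scope holds. Noninferiority is hypothesised for upper airway events in general, while the design supports it for intraoperative cough only; LS, CE and LSE cannot carry a noninferiority conclusion as planned. This rests on the text alone and on no numerical assumption. It limits what the trial may conclude on a secondary aim and leaves the emergence-time endpoint untouched.

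No conclusion that the trial is underpowered for the joint cough claim follows. Joint power is about 0.999 with the stated margin of 0.20, or 0.69 to 0.83 with the margin of 0.10 that generates 81 and 112. All these figures assume 112 evaluable patients per group, equal true cough rates and a one-sided level of 0.05. Because the stated margin and the stated sample size do not belong together, neither joint power figure can be entered in the protocol yet.

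**What to change.** 1. In the Abstract and in Objectives and study design, limit the noninferiority claim to intraoperative cough, and use that one name for CO throughout.
2. Say that a claim against both sevoflurane and propofol needs both upper confidence bounds below the margin. Because both must succeed, no alpha split is needed. Use *and* consistently.
3. Report LS, CE and LSE as risk differences with confidence intervals, without a noninferiority claim. If such a claim is wanted, give each event its own justified margin before unmasking.
4. Reconcile the margin and the per-group numbers in Sample size, and only then state joint power. Do not write 0.69 to 0.83 beside a margin of 0.20.

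Items 1 to 3 cost wording and a narrower headline, and no added patients. Item 4 also costs only wording if 0.20 is confirmed. If 0.10 is confirmed, the sponsor would either accept the lower joint power or, for 0.80 at p = 0.10, need 143 evaluable patients per group instead of 112.
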